### Interventions

#### Intervention group: self-management program (SEMPO)

The SEMPO program was developed by experienced clinicians and researchers and is based on well-known principles from the self-management concept and established rehabilitation strategies [11, 46]. Thus, SEMPO adheres to theories of self-efficacy as a mean of coping [11, 47]. The program aims to enhance self-efficacy by strengthening patients’ skills and confidence in managing the persisting consequences of the injury, as well as enhancing their health literacy and problem-solving competence. The program integrates components from evidence-based rehabilitation strategies within relevant functional domains [48, 49] to fit the symptom burden of the trauma population. User involvement was an essential part of the development of the intervention, and we collaborated with a user panel consisting of persons living with persistent injury-related consequences and representatives from the involved user organization, the National Association of the Traumatically Injured (LTN). In addition, the program has been adjusted after feedback from a test trial of the intervention (*n* = 5 persons), where patients were interviewed at the end of the testing regarding perceived usefulness and feedback on program content.

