### Sample size

The sample size was estimated based on the primary outcome, the Trauma Coping Self-Efficacy Scale questionnaire [26]. The questionnaire is a 9-item scale answered on a scale ranging from 0 (not capable) to 7 (totally capable). A mean difference in the Trauma Coping Self-Efficacy Scale of 0.6 between baseline and follow-up between the groups is considered as a clinical relevant difference (ref). In order to detect a mean between-group difference of 0.6 with an estimated standard deviation of 1, equal allocation to both groups, 80% power, and a significance level of 5%, we will need to include a minimum of 45 patients in each group and a total of 90 participants [51]. With an assumed attrition rate of 20%, 110 patients will be included (i.e., 55 patients in each group). The sample size calculation was done based on the classical randomization arm (RA), and we aim to achieve the same power in the self-selection (SA) arm. However, the SA is considered an exploratory part of this study to evaluate the influence of patients’ treatment preferences. According to a previous longitudinal study at OUH, approximately 310 patients with trauma-related disability from 18 to 72 years of age may meet the inclusion criteria [52]. Based on previous studies, approximately 70–80% will be eligible for inclusion, resulting in 218–249 eligible patients per year.

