### Allocation/randomization

#### Sequence generation and allocation concealment mechanism

The allocation sequence will be computer-generated by VieDoc using permuted blocks with varying block sizes. Patients will be randomized immediately after baseline assessment to RA or SA (see Fig. 1). Patients allocated to the RA will further be randomized to the intervention and control group, while patients randomized to the SA will self-select allocation to either intervention or control group.

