### Statistical methods

Sociodemographic, clinical, and injury-related characteristics and outcome data will be presented using descriptive statistics. Independent sample *t*-test will be used for between-group mean comparisons for normally distributed continuous data, and Mann–Whitney *U*-tests for skewed data. For comparison of categorical data, chi-square tests or Fisher’s exact test will be used. To investigate the effectiveness of the intervention on self-efficacy, symptom burden and disability, and patient impression of change, mixed-effect models will be used to account for repeated measurements by patients. Time and time-by-treatment interaction will be used as fixed effects in these models. The linear mixed effects model will give estimated mean values for all time points (T1, T2, T3, and T4), changes from baseline, and between-group differences from baseline with 95% confidence intervals. The models will first be performed separately within the classical RCT and self-selected groups, and if reasonable, merged together. Possible confounders or mediators will be included when analyzing the self-selected group. To reduce the risk of dropout bias, the analyses will be based on an “intention to treat” principle by analyzing all patients in the group they were randomized to, regardless of whether they participated in or completed the intervention. A significance level of 5% will be used.

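### The self-selection model puts mediators on the same footing as confounders, so its estimate of SEMPO's effectiveness could lose the mediated part of the effect

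*Protocol article*

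**What the plan says.** All of the modelling is set out in one paragraph of the protocol article, under Statistical methods.

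- Purpose: "To investigate the effectiveness of the intervention on self-efficacy, symptom burden and disability, and patient impression of change, mixed-effect models will be used".
- Structure: "Time and time-by-treatment interaction will be used as fixed effects in these models".
- Reported result: "changes from baseline, and between-group differences from baseline with 95% confidence intervals".
- Order of work: "The models will first be performed separately within the classical RCT and self-selected groups, and if reasonable, merged together".
- Covariates in the SA arm: "Possible confounders or mediators will be included when analyzing the self-selected group".

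The covariate sentence names no variable and does not limit the covariates to baseline values. No direct or indirect effect is defined anywhere in the article.

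Three other places bear on the sentence. The section on sequence generation says that "patients randomized to the SA will self-select allocation to either intervention or control group". The Sample size section says that "the SA is considered an exploratory part of this study to evaluate the influence of patients’ treatment preferences". The description of the SEMPO intervention lists, among the programme's aims, self-efficacy, skills and confidence, "as well as enhancing their health literacy and problem-solving competence". Table 2 schedules health literacy, communication with physicians and self-efficacy at T1 to T4.

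**The concern.** A confounder in the SA arm is a pre-choice variable that influences both the choice of SEMPO and the outcome. It has to be adjusted for. A mediator comes after the choice and carries part of the programme's effect to the outcome. Conditioning on it in a model meant to give the overall effectiveness of SEMPO does two things:

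- It removes the part of the effect that passes through the mediator.
- It opens a path through any unmeasured common cause of mediator and outcome, which can bias what remains in either direction.

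What is at stake is the meaning of the SA estimate. One stated aim of the arm is to explore whether preference influences the intervention's results. That needs SA and RA estimates of the same quantity. The covariate sentence applies to the SA arm only, so mediator adjustment would make the two differ by construction. A smaller SA effect might then be read as a finding about preference when it comes from over-adjustment. If the arms were merged with these covariates, the pooled estimate would have the same fault.

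This is more than a missing covariate list, which an analysis plan could supply. It is a stated rule that an analysis plan following the protocol would carry forward.

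**Working it through.** **1. The plan's own figure.** From Sample size: difference 0.6, SD 1, equal groups, 80% power, 5% level (taken as two-sided). The normal formula gives n = 2 × (1.960 + 0.842)² × 1² / 0.6² ≈ 43.6, so 44 per group. The t-test version gives 44.6, so 45, which is the stated number. The point disputes no figure; 0.6 is used below only as a yardstick.

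**2. Simple attenuation.** If a share p of the total effect runs through the adjusted mediator, and there is no other bias, the treatment coefficient is 0.6 × (1 − p).

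- p = 0.30: 0.6 × 0.70 = 0.42
- p = 0.50: 0.6 × 0.50 = 0.30

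The shares are assumptions. This step restates them on the outcome scale and predicts nothing about this trial.

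**3. Simulation with self-selection.** One linear model at a single endpoint stands in for the mixed model, with 400,000 subjects per scenario. The structure and coefficients are assumed:

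- C is a baseline confounder. The log-odds of choosing treatment A are 0.8 × C.
- Mediator: M = 0.6·A + g·U + noise, where g·U and the noise together have variance 1. U is unmeasured.
- Outcome: Y = 0.6(1 − p)·A + p·M + 0.3·C + g·U + noise. The total effect of A is 0.6(1 − p) + 0.6p = 0.6.

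Once A and C are accounted for, what remains of M has variance 1 and covariance g² with g·U. The coefficient of M is therefore p + g² instead of p, and the coefficient of A falls to 0.6(1 − p) − 0.6g². The last term is 0.054 at g = 0.3 and 0.15 at g = 0.5.

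| Assumed share p | C only | C + M, g = 0 | C + M, g = 0.3 | C + M, g = 0.5 |
|---|---|---|---|---|
| 0.25 | 0.60 | 0.45 | 0.39 | 0.29 |
| 0.50 | 0.60 | 0.30 | 0.24 | 0.15 |
| 0.75 | 0.60–0.61 | 0.15 | 0.10 | 0.00 |

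The simulated values agree with the formula to within about 0.01. Adjusting for the confounder alone recovers 0.6 in every scenario (0.596 to 0.608). With no adjustment the estimate is about 0.81. So confounder adjustment is needed, and only the mediator part of the sentence is wrong. Here U acts in the same direction on mediator and outcome; with opposite directions the g² term changes sign.

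**4. Does another section cure the wording?** The process evaluation sections speak of moderators, fidelity and contextual factors. They set up no mediation analysis to which the sentence could refer.

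**5. Are pre-choice values available?** Trial design and Data collection methods place the T1 assessment before any randomization, and so before the SA patient chooses. T1 values can serve as confounders; values from T2 onward cannot.

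**The case against.** The strongest reply concerns reach. The SA arm is repeatedly called exploratory. The sample size rests on the randomized arm, and the covariate sentence does not apply there. Merging is conditional, follows the separate models, and is not said to carry these covariates. All of this stands. It limits the severity but does not make the rule correct.

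A second reply is that the plan commits to nothing harmful. It names no mediator, says only that such variables are possible, and has T1 values for every candidate scale. Entering T1 health literacy would be ordinary confounder adjustment. That also stands as far as it goes. But a baseline value used in that way is a confounder, and the sentence allows mediators in addition. Open discretion over post-choice covariates offers no protection.

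A third reply is that the word may be a slip for moderators, which the process evaluation uses, or shorthand for exploratory mediation work. Either is possible. In both cases the sentence still needs changing: moderators enter as treatment interactions, and mediation needs its own analysis and assumptions.

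A reader might infer that the plan itself designates health literacy and problem-solving as mediators. It does not. The intervention section lists programme aims, and Table 2 contains no problem-solving measure. A reader might also count self-efficacy among the mediators in the main model. It is the primary outcome and cannot mediate the effect on itself; it could play that role only for secondary outcomes.

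**Conclusion.** The point holds with moderate severity. As written, the protocol allows mediators into a model meant to give the effectiveness of SEMPO among self-selecting patients, and nothing else in the article corrects this. If post-choice values of variables that SEMPO aims to change were entered, the estimate would lose the mediated part, could gain further bias, and would not be comparable with the RA estimate.

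The documents give no basis for sizing the loss. The 0.42–0.30 range rests on an assumed mediated share of 30–50% and on taking 0.6, the difference regarded as clinically relevant, as the true effect. The table above also assumes the strength of confounding.

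Two stronger conclusions are tempting and are not supported. One is that the trial's primary result is compromised. The randomized comparison is untouched, and the main result could be affected only through a merged model that carries these covariates. The other is that the SA arm loses its whole purpose. Comparison of effects is one of its stated aims, beside adherence and attrition, and outcome-model covariates do not alter those.

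**What to change.** In Statistical methods, delete *or mediators*. State that the SA model, and any merged RA and SA model, will adjust only for confounders measured at T1, before the choice is made. Candidates are already collected: age, sex, education, comorbidity, injury severity and T1 symptom scores. The exact list can be left to the analysis plan.

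If mediation is of interest, describe it as a separate, labelled exploratory analysis with its own target quantity and assumptions. If moderators were meant, say so and enter baseline moderators as interactions with treatment.

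The cost is one or two sentences and no new data. The article estimates that recruitment will run to the end of 2026, so the change can be made before the final analysis.

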### Process evaluation analysis

We will conduct a process evaluation to investigate potential moderators of outcomes, such as intervention delivery, fidelity, and acceptability. The participation rate, numbers of consultations, the direct and indirect time related to each consultation, the kinds of problems presented, completion of intervention according to protocol, and any reasons for noncompliance will be assessed. Ten percent of intervention sessions will be overseen by a senior researcher aiming to evaluate treatment fidelity. Any need for adjustments with regard to adherence will be discussed in regular project meetings. We will also evaluate the experiences with the intervention for participants and therapists. The patients in the intervention group will rate intervention usefulness on a scale from 1 to 5 (not useful to extremely useful) and complete a semi-structured questionnaire about satisfaction with program content. After completion of the intervention, the therapist will rate the participant’s acceptability on a therapist checklist, by rating the degree of participation, interaction, and skill attainment on a scale from 0 to 3. The role of contextual factors will be explored in regression analysis, i.e., exploring external factors that may play into intervention effects.

### Additional analysis

#### Subgroup analysis

To acknowledge patient outcome preferences, we will also perform subgroup analysis based on the outcome preferences to identify which validated questionnaires can be considered as preferred patient-centered outcome measures in this or similar intervention studies, and whether the intervention might be more efficient on some problem domains than others.

#### Health economics analysis

Cost-effectiveness and cost-utility analyses of SEMPO compared to standard of care will be based on the effectiveness, measured by self-efficacy, symptom burden, global functioning, and quality-adjusted life years (QALYs). Use of healthcare and social support services (categories of service, quantities, and unit costs) collected during the study period, will be used to estimate total costs according to groups. In addition, vocational and educational rehabilitation, equipment and assistive technology, income, and informal care provided by family and significant others will be registered. We will estimate clinical effectiveness in QALYs using standardized conversion tools to convert health benefits into an index of HRQoL, as measured by EQ-5D [40]. Further, simulated cost consequences of the program will be considered from both a healthcare and societal perspectives [55]. Based on the estimated costs and QALYs, we will estimate the incremental cost-effectiveness ratio (ICER), defined as the differences in costs of the SEMPO and standard of care, relative to differences in QALYs of SEMPO and standard of care. Uncertainty will be presented by bootstrapping.

#### Managing non-adherence and missing data

Missing data will be handled according to the scoring manuals of the outcome measurements and by imputation. A sensitivity analysis will be performed to identify differences in patients’ characteristics between complete cases and dropouts.

### Monitoring

No data monitoring committee will be established for this trial because the trial does not include a pediatric population, has no potential to harm patients, will be performed in a short time frame, and is limited to a single center. Any substantial change to the study design affecting ethical or data protection issues will be reported to the Norwegian Regional Committee for Medical and Health Research Ethics (REK) and the Data Protection Office at OUH, respectively.

#### Adverse event reporting and harms

Any adverse events will be documented and reported by the project leader to the project owner, the Data Protection Office at OUH, and the ethical committee that have approved the study.

#### Auditing

No formal auditing is planned for this study. However, the Project Management Group will hold regular meetings to review the study process and implement necessary corrections as needed. Additionally, the extended project group, which includes all collaborators, will convene approximately twice a year to discuss the timeline and study progression. The steering committee will hold meetings twice every 6 months, to ensure progress and oversee conduct.

### Ethics and dissemination

#### Research ethics approval

The study has been approved by the Norwegian Regional Committee for Medical and Health Research Ethics (REK) (REK number 614625) and the Data Protection Officer at OUH. The study and all procedures will be conducted according to the declaration of Helsinki [56]. Information about participants will be handled by healthcare professionals adhering to Norwegian law on confidentiality. Informed consent will be obtained providing information about the right to withdraw from the project without giving any reason and without consequences for treatment access. Signed written informed consent forms will be collected from all participants by the PhD fellows. The involved user organization, the National Association of traumatically injured, LTN [57]will also take part in the monitoring and management of the research process.

#### Protocol amendments

As a preparation to the RCT, we will conduct a feasibility study, and necessary adjustments to the protocol will be discussed and decided in project group meetings and reported to the REK committee and the Data Protection Office at OUH. Changes in study procedures will be tracked and reported to investigators, trial registers, and health professionals working in the study.

#### Dissemination policy

The project aims to publish scientific papers in both national and international peer-reviewed journals. We expect to publish in high-quality scientific journals within the field of trauma rehabilitation due to the innovative aspects of the study and the important knowledge it contributes to enhancing post-acute treatment and rehabilitation following traumatic injuries. Findings will be presented at national and international scientific conferences, workshops and symposia, and to local and national clinical audiences. The study findings will be disseminated through the channels of the user organization. For study participants, we will create a lay abstract of the main findings. The dissemination reports and all papers will be written following the Consolidated Standards of Reporting Trials (CONSORT) to ensure transparency in reporting of the RCT [58]. In accordance with Norwegian Data Protection Laws, the data set will not be made available to the public. Anyone wishing to view the original data can do so by request to the corresponding author and physical presence at Oslo University Hospital, Norway.

## Discussion

This self-management intervention study targets patients with moderate to severe physical trauma in the sub-acute phase and patients at risk of long-term symptom burden and injury-related disabilities. The innovative and newly designed self-management program; SEMPO is a complex intervention and entails ingredients aiming to enhance patients’ self-efficiency in managing difficulties they experience in daily life in the sub-acute phase following injury. The program includes therapeutic ingredients such as psychoeducation, action planning, training in problem-solving, and peer-sharing experience in managing injury-related consequences. The program focuses on establishing and reviewing personal action plans, facilitating individual skills enhancement, and sharing experiences to enhance social encouragement. To our knowledge, this is the first study to investigate the effect of a self-management program tailored to patients with moderate to severe physical trauma in the sub-acute phase of recovery. It is also the first study to bring the self-management concept into a structured and manualized group-based intervention in the trauma population. The intensity of the program, with eight weekly sessions, allows thorough training in goal setting and adaptive management of difficulties. The intervention is in line with person-centered treatment.

The inclusion of a self-selection arm in a pragmatic RCT is an innovative way to incorporate the influence patients’ preferences have on the effectiveness of the intervention. This approach brings the experimental design for clinical interventions closer to real-world scenarios and aligns with the notion of shared decision-making. The self-selection arm is an explorative part of the study, while the classic randomization arm (patients allocated by randomization to either intervention or control group), will follow a more traditional rigorous experimental design.

### Limitations

This is a pragmatic clinical trial and blinding of patients and therapists is not feasible. However, outcome assessors will be blinded to group allocation. The treatment as usual may potentially vary based on demographic factors, as well as injury-related factors. Treatment as usual is not standardized in the study, but it does reflect the real differences in treatment access and availability. Another possible limitation is the risk of non-adherence and dropouts at follow-up and potential differential drop-out according to group allocation and/or etiology. To facilitate study adherence and prevent drop-outs, the research team will be well-trained, conduct outreach and offer flexibility regarding timing and intervention delivery (e.g., self-selection of face-to-face mode or telehealth delivery).

### Trial status

Protocol version 1.0. Recruitment for the RCT began in January 2024 and will continue until target sample size has been reached, estimated by the end of 2026.

## Data Availability

In accordance with Norwegian Data Protection Laws, the data set will not be made available to the public. Anyone wishing to view the original data can do so by request to the corresponding author and physical presence at Oslo University Hospital, Norway.
